#### 2.3.3. Data Collection

Outcome quantitative measures will be completed by all parents in two assessment periods, namely, baseline and post-intervention. In addition, participants from the intervention arm will have a third assessment period, namely, a 6-month follow-up. Primary caregivers with multiple children will be asked to designate a target child for whom they will complete the measures. They will be advised to select the child who they have more concerns about in terms of behavioral difficulties. In the cases where both parents from a family unit participate, Parent 1 (i.e., the first caregiver to sign in to the program) will choose the target child. Parent 2 will be notified of the age of the target child by the research team and will be asked to complete the questionnaires while thinking of this child. Researchers will also advise Parent 2 to confirm the name of the child selected as the target with Parent 1.

Measures will be completed through an online survey created on Qualtrics.com and have an estimated completion duration of 20 min. Parents will have a maximum of two weeks to fill out the survey in each assessment period. Qualitative interviews will be conducted post-intervention in person in a research setting. Parents who participated in the Being a Parent program will be asked to take part in the interview and all that accept will be included. The interview will follow a pre-designed guide, consisting of an average of 20 questions and 35 associated probes, to explore parents’ experiences with the intervention and its feasibility (e.g., “*What did you think about the homework assignments*”, “*Did you ever considered quitting the program?*”, “*What were the benefits of the program?*”, “*What are your opinions about the group leaders?*”). This interview will have an average duration of 1.5 h and will be recorded with a recorder owned by the interviewer. Parents will also be advised not to share any personal information that may identify them during the interview.

#### 2.3.4. Incentives

Families will receive monetary incentives (i.e., vouchers) from a national supermarket. Each family will receive a EUR 5 voucher for each assessment completed, regardless of their assigned study arm. Families who complete both the baseline and post-intervention measures will also qualify for entry into a draw for a chance to win a EUR 200 voucher. At the 6-month assessment, families will have the opportunity to enter another draw for a EUR 20 voucher. No monetary incentives will be delivered for completing the qualitative interviews. The primary goal of providing these monetary incentives is to promote the completion of assessment measures.

#### 2.3.5. Ethical Considerations

This project has been approved by the Ethics Committee from Ispa—University Institution [D-054-11-22] and is registered on ClinicalTrials.gov [NCT05626244]. Data collected will be confidential, and parents will be given a unique identification number in order to guarantee that the questionnaires and the interviews do not contain any information that may identify them. Furthermore, in compliance with the General Data Protection Regulation (GDPR), personally identifiable information will be securely stored separately from outcome data. Additionally, surveys and recordings will be stored for a period of five years, after which they will be permanently deleted.

Ethical considerations guided the provision of vouchers, and the prespecified monetary value was deemed sufficient to acknowledge the commitment of families without exerting undue influence on their decisions. Participants will be transparently informed of the incentive structure before informed consent is requested.

### 2.4. The Portuguese Being a Parent Program

The Being a Parent intervention is part of the Empowering Parents, Empowering Communities program developed in the United Kingdom (UK) by the Centre for Parent and Child Support at South London and Maudsley NHS Foundation Trust (SLAM) and the Child and Adolescent Mental Health Services (CAMHS) Research Unit at King’s College London. It consists of eight weekly sessions plus an optional introductory session, each with a duration of two hours, facilitated by two accredited parents of the community and directed at groups of seven to twelve parents [18].

Built on attachment theory, family systems theory and cognitive–behavioral frameworks, it is rooted in empirically validated parenting strategies that specifically address the most common issues present in children aged two to eleven years old with behavioral problems [19]. Each session is characterized by its high degree of interactivity, featuring a dynamic combination of small and large group discussions, role-playing, demonstrations, the sharing of experiences, and reflective exercises [19]. Table 1 describes in detail the content discussed in each session.

Adapting the Being a Parent intervention to the Portuguese community encompassed pertinent cultural and delivery changes. Following a stacked intervention adaptation model, namely, the Ecological Validity Model (EVM) [23,26] and the Cultural Adaptation Process (CAP) [27], the Being a Parent program was translated to Portuguese, and minor changes related to linguistic features were implemented in order to culturally adapt the intervention. No content modifications were made due to the fact that all topics and exercises were considered pertinent to the Portuguese context, despite cultural differences that may exist. Due to legal aspects, the main modification in the Portuguese version was focused on program delivery. Instead of using a peer-led approach, the Portuguese version will be professionally led, meaning that two accredited psychologists with experience in child and familial problems will deliver the intervention.

Moreover, the parenting program will be delivered face to face in a university setting, namely, at Ispa—University Institution (Lisbon). To ensure a comprehensive experience of the program and its processes, a minimum of five members per group will be required to start the intervention. Parents will complete the program and receive a participation certificate if they attend at least six sessions. Babysitting services will be provided in all sessions, allowing parents to bring their child while they attend the program. Two accredited psychologists will deliver the program to all groups.

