### 2.7. Sample Size

Sample size calculation was based on the CONSORT 2010 statement extended to feasibility trials [35] and the Lewis et al. [36] methodology. This approach calculates sample size by conducting hypothesis testing based on estimations of predefined feasibility outcomes being within the unacceptable “red zone” (null hypothesis) and contrasting this with an alternative hypothesis of being within the “favorable” green zone [35]. A sample size is considered appropriate if it allows for ≥80% power to reject being in the red zone if the green zone holds true. For detailed information about this methodology, please consult Lewis et al. [36].

Progression parameters and their subsequent point estimates as described in Table 2 were used. Considering a one-tailed, one-sample binomial test based on normal approximation (with continuity correction) with α = 0.05, the following minimum sample sizes for each parameter were obtained:Feasibility of participant retention at post-intervention (Rul = 0.50 and Gll = 0.70)—41 participantsFeasibility of consent rate (Rul = 0.40 and Gll = 0.60)—42 participantsFeasibility of program completion (Rul = 0.45 and Gll = 0.75)—18 participants (intervention arm)Feasibility of program acceptability (Rul = 0.45 and Gll = 0.75)—19 participants (intervention arm)Feasibility of program fidelity (Rul = 0.40 and Gll = 0.70)—19 participants (intervention arm)

Therefore, a sample size of 42 participants, with 25 participants in the intervention arm, allows for ≥80% power to reject the null hypothesis for each of the feasibility outcomes. Moreover, this sample size is sufficient for the estimation of effect sizes for a future larger trial, as it allows for the collection of preliminary data needed to calculate reliable effect size estimates and assess the variability in psychological measures.

Regarding our qualitative data, according to the recommendations of Boddy [37] and van Risjnsoever [38], we aim to recruit 10 to 12 participants, as this sample size is often sufficient to achieve data saturation when the aim is to explore shared experiences within a relatively homogeneous group. Moreover, we will closely monitor data saturation during analysis and will adjust the sample size if necessary to ensure robust and meaningful findings.

**Table 2 healthcare-13-00176-t002:** Feasibility progression parameters.

Parameter	Thresholds		Justification

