1. Feasibility of Retention of Families at Post-Intervention *Can a significant number of recruited families be retained until post-intervention?*	GREEN ZONE (Go—Proceed with full RCT)	>70%	Ensuring a substantial post-intervention retention rate is essential to obtain accurate and unbiased post-intervention data Favorable retention rates at the feasibility trial will contribute to estimating the required sample size for a larger RCT Systematic reviews have shown that attrition rates between 9 to 27% can be found in RCTs testing parenting interventions for childhood behavior problems [39] Previous trials of the BaP program reported an average retention rate of 80% [18,19]
	AMBER ZONE (Amend—Proceed with changes)	50–70%	
	RED ZONE (Stop—Do not proceed unless significant changes are made)	<50%	
2. Feasibility of Consent Rate *Is the rate of eligible families who consented and were randomized favorable for a large-scale RCT?*	GREEN ZONE (Go—Proceed with full RCT)	>60%	An adequate consent rate is essential for the feasibility trial to accurately estimate the number of families who need to be reached, in order to achieve the required sample size to obtain significant statistical power in a large-scale RCT. Low consent rates may provide important information regarding issues in recruitment procedures (such as locations of recruitment or information available to interested participants). Previous trials report an average consent rate of 70% [40] Previous trials of parenting interventions in Portugal report consent rates ranging from 63% to 97% [41,42] Previous studies of the BaP program report an average consent rate of 71% [19]
	AMBER ZONE (Amend—Proceed with changes)	40–60%	
	RED ZONE (Stop—Do not proceed unless significant changes are made)	<40%	
3. Feasibility of Program Completion *Can a significant number of participants from the intervention arm complete the BaP program?*	GREEN ZONE (Go—Proceed with full RCT)	>60%	Achieving favorable program completion rates is critical to obtain accurate and unbiased data A systematic review [43] found a mean program completion rate of 80% with a wide variety across studies between 50% and 100% Previous trials of the BaP program have shown an average completion rate of 70% [18,19]
	AMBER ZONE (Amend—Proceed with changes)	30–60%	
	RED ZONE (Stop—Do not proceed unless significant changes are made)	<30%	

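### Program completion is sized in section 2.7 on red/green limits of 45%/75%, but Table 2 sets 30%/60% for the same parameter

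*Protocol article*

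**What the plan says.** - **Definition (section 2.4).** "Parents will complete the program and receive a participation certificate if they attend at least six sessions". This section gives no limits and nothing in it is wrong.
- **Source of the limits (section 2.7).** "Progression parameters and their subsequent point estimates as described in Table 2 were used".
- **Method (section 2.7).** "one-tailed, one-sample binomial test based on normal approximation (with continuity correction) with α = 0.05", with this adequacy criterion: "A sample size is considered appropriate if it allows for ≥80% power to reject being in the red zone if the green zone holds true".
- **Completion line (section 2.7).** Red upper limit 0.45, green lower limit 0.75, 18 participants in the intervention arm.
- **Acceptability line (section 2.7).** "Feasibility of program acceptability (Rul = 0.45 and Gll = 0.75)—19 participants (intervention arm". The limits are the same as on the completion line, but n is one higher.
- **Table 2, parameter 3.** The question is "Can a significant number of participants from the intervention arm complete the BaP program", with green above 60%, amber 30–60% and red below 30%. The justification column adds: "Previous trials of the BaP program have shown an average completion rate of 70" (per cent).
- **Decision (section 2.8.3).** Progression to a large-scale RCT is judged on five parameters with three zones, and the reader is sent to Table 2 for the threshold values.

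**The concern.** Section 2.7 says it uses the Table 2 values, and for retention (50/70), consent (40/60), acceptability (45/75) and fidelity (40/70) it does. Only completion differs: 45/75 in one place and 30/60 in the other. There is also an error visible within section 2.7 alone, because one formula with one alpha and one power cannot return both 18 and 19 from the same pair of limits.

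The zones are what a feasibility trial delivers, because they decide whether a full trial follows. The two pairs disagree for observed completion of 30–45% (Amend or Stop) and of 60–75% (Go or Amend). The second range contains the 70% that the plan itself cites from earlier trials of the program. As printed, the power statement for completion also refers to a different hypothesis pair from the one Table 2 would judge.

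**Working it through.** **Inputs.** One-sided alpha 0.05 (z = 1.645), power 0.80 (z = 0.842), and a normal approximation with continuity correction, all from section 2.7. Limits p0 (red) and p1 (green) come from section 2.7 and Table 2; d = p1 − p0.

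**Formula.**
n0 = [(1.645·√(p0(1−p0)) + 0.842·√(p1(1−p1))) / d]²
n = (n0/4)·[1 + √(1 + 2/(n0·d))]²

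**Reproducing the plan's figures**

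| Parameter | p0/p1 | n0 | n with correction | Nearest integer | Printed |
|---|---|---|---|---|---|
| Retention | 0.50/0.70 | 36.49 | 41.34 | 41 | 41 |
| Consent | 0.40/0.60 | 37.10 | 41.95 | 42 | 42 |
| Completion, Table 2 limits | 0.30/0.60 | 15.11 | 18.29 | 18 | 18 |
| Completion, section 2.7 limits | 0.45/0.75 | 15.54 | 18.73 | 19 | 18 |
| Acceptability | 0.45/0.75 | 15.54 | 18.73 | 19 | 19 |
| Fidelity | 0.40/0.70 | 15.77 | 18.96 | 19 | 19 |

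All five printed sizes come back with rounding to the nearest integer, provided completion was computed on 0.30/0.60. With 0.45/0.75 the completion line would read 19, as the acceptability line does. Retention shows that the rounding was not upwards (41.34 became 41).

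**Power by the same approximation**

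| n in intervention arm | 0.30/0.60 | 0.45/0.75 |
|---|---|---|
| 18 | 79.4% | 78.2% |
| 19 | 81.5% | 80.7% |
| 21 (1:1 split of 42) | 85.2% | 84.9% |
| 25 (stated in 2.7) | 90.6% | 91.0% |

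**How far the two pairs disagree.** Let X be the number of completers, binomial(n, p), and place X/n in the zones of each pair.

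With n = 21:
- 30/60: Stop for X ≤ 6 (6/21 = 28.6%), Amend for 7–12, Go for X ≥ 13 (13/21 = 61.9%).
- 45/75: Stop for X ≤ 9 (9/21 = 42.9%), Amend for 10–15, Go for X ≥ 16 (16/21 = 76.2%).
- The zone differs for X = 7–9 and X = 13–15.

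With n = 25, the zone differs for X = 8–11 and X = 16–18.

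| True completion | n | Quantity | 30/60 | 45/75 |
|---|---|---|---|---|
| 70% (cited benchmark) | 21 | P(Go) | 0.85 | 0.36 |
| 70% | 25 | P(Go) | 0.81 | 0.34 |
| 40% (illustrative) | 21 | P(Stop) | 0.20 | 0.69 |
| 40% | 25 | P(Stop) | 0.15 | 0.73 |

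At a true 70% with n = 21, the two pairs give different zones with probability 0.50.

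**The case against.** The strongest reply is that the plan has one decision rule and names it. Section 2.8.3 sends the reader to Table 2 for the thresholds, section 2.7 itself defers to Table 2, and section 2.7 assigns no Go, Amend or Stop; its limits are inputs to a power calculation. On that reading the completion line is a copying slip, and the printed 18 already belongs to Table 2's limits. Most of this stands. A reader might infer that the trial has two competing operative rules. The documents do not support that: 2.7 holds a conflicting sizing input. The reply does not remove the contradiction, though. The 45/75 pair is printed as the completion hypothesis, and nothing in the text says it is an error.

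A reader might also infer that 18 fits neither pair, so that completion is underpowered. That goes too far. Rounded up strictly, both pairs need 19, but 18 is the nearest integer to 18.29 for 0.30/0.60, under the rounding seen for retention. The shortfall at 18 is 0.6 points of power for 30/60 and 1.8 for 45/75. Exact binomial power at 18 is lower, but the plan specifies the normal approximation. The arm will in any case hold 21 or 25. Nor is it sound to test 2.7's red limit against Table 2's green limit and call the result a power deficit, because neither place proposes that mixed pair.

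Finally, the zone probabilities compare Table 2 with a pair that is probably a slip. They show what is at stake if the wrong pair is read; they do not predict the trial's result.

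**Conclusion.** The contradiction is real and confined to one parameter: the completion limits in section 2.7 (45/75) do not match Table 2 (30/60), although 2.7 says they do. The arithmetic indicates that 18 was computed on Table 2's limits and that 0.45/0.75 came from the acceptability line. That is an inference, and only the authors can confirm it.

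The limits matter for the progression decision. At the cited 70% completion with 21 in the arm, P(Go) is 0.85 or 0.36 depending on the pair. These probabilities assume independent participants, the whole arm in the denominator, and zones applied to the observed proportion. The planned sample size is not affected, since 21 or 25 in the intervention arm gives about 85–91% power for either pair. Which of 21 and 25 is meant is a separate question, and this conclusion does not depend on it.

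**What to change.** Before any post-intervention data are seen, use one pair of completion limits in both places.

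- **If Table 2 is as intended**, which section 2.8.3 supports: change the completion line in section 2.7 to Rul = 0.30, Gll = 0.60, n = 19 (18.29 rounded up; power 81.5%).
- **If 45/75 was intended**: change the Table 2 completion row to red below 45%, amber 45–75%, green above 75%, and the n in section 2.7 to 19 (18.73 rounded up; power 80.7%).

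The authors should record which pair was meant. The cost is one line of section 2.7, or one row of Table 2 plus the n. No extra participants are needed, because 21 or 25 in the intervention arm already exceeds 19.

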### 2.5. Control Condition

Families randomized to the control group will be in a waitlist condition. Hence, participants will not receive any active treatment in parallel with the intervention arm but will have the opportunity to subsequently take part in the Being a Parent program.

The choice of the control condition was guided by several considerations. Firstly, to the best of our knowledge, there are no current “standard of care” parenting interventions for childhood behavior problems in Lisbon or Setúbal, and thus, comparing the Being a Parent program with an active control group is not feasible. Moreover, given the limited availability of support in the community, the inclusion of a waitlist condition will enable us to extend intervention to all participating parents.

### 2.6. Measures

#### 2.6.1. Feasibility, Fidelity, and Acceptability

Structured sheets will be used to record significant feasibility parameters associated with trial methodology and program implementation. This will enable the assessment of participants’ rates related to (a) enrolment; (b) eligibility; (c) intervention attendance and retention; and (d) data collection. Dropout will also be recorded for both arms, as well as missed sessions for the experimental group. The research team, with the help of the group leaders, will fill out weekly review forms to assess fidelity criteria (e.g., the delivery of content; alignment with intervention methods and strategies). In addition, a treatment acceptability rating scale (TARS) created by the Empowering Parents, Empowering Communities team will be completed by the participants from the experimental group post-intervention. This scale was specifically created in order to assess the unique aspects of treatment acceptability that are specific to the Being a Parent program. It comprises 12 tailored items in which parents will report on satisfaction with intervention delivery. Questions reflect the content and delivery style of this specific parenting program, ensuring that the assessment is both contextually relevant and comprehensive (e.g., “*In general, are you satisfied with group leaders?*”).

A qualitative semi-structured interview will also be conducted post-intervention with a small sample of the participants from the experimental group. The main goal is to better understand the experiences of parents that participate in the parenting program. Therefore, topic guides will include open prompts regarding (a) trial implementation (e.g., recruitment and data collection); (b) intervention implementation (e.g., localization and dates); (c) intervention acceptability (e.g., content and impact); and (d) the adequacy of group leaders (e.g., competencies).

#### 2.6.2. Psychological Outcomes

The following self-report questionnaires will be completed by parents through an online survey at baseline, post-intervention, and at follow-up. These measures were carefully chosen to provide a well-rounded understanding of the child’s behavioral challenges, parenting styles, and the parents’ sense of competence, all of which are central to the intervention’s goals. All participants will also complete a sociodemographic questionnaire at baseline designed specifically for this trial.

Child Behavior Checklist for Preschool and School Years (CBCL) [28,29]. This is a self-report measure that is completed by caregivers of children between the ages of 1.5 and 18 years old [29]. It consists of different statements describing various behavioral and emotional problems, and caregivers must rate the extent to which each statement applies to their child. Only the Externalizing Scale (the Attention Problems, Aggressive Behavior, and Delinquent Behavior in the school years version—33 items) and the subscale Anxiety/Depression (12 items) will be used.Parenting Styles and Dimensions Questionnaire (PSDQ) [30,31]. This is a self-report questionnaire designed to assess different parenting dimensions and three main styles, namely, authoritative, authoritarian, and permissive [31]. Parents must rate their agreement or disagreement with statements about their parenting strategies [31].Parental Concerns Scale [32]. Divided into five concern dimensions, this evaluates main domains of parental concerns, namely, family and school problems; eating, sleep, and physical complaints; preparation; fears; and negative behaviors [32].Parenting Sense of Competence (PSOC) [33,34]. An adapted version for at-risk parents of Parenting Sense of Competence will be used to assess parents’ feelings of competence in their parenting roles [34]. It comprises two subscales, namely, Satisfaction and Efficacy [34].

All measures have been adapted to and validated in Portugal and present adequate psychometric properties.

### 2.7. Sample Size

Sample size calculation was based on the CONSORT 2010 statement extended to feasibility trials [35] and the Lewis et al. [36] methodology. This approach calculates sample size by conducting hypothesis testing based on estimations of predefined feasibility outcomes being within the unacceptable “red zone” (null hypothesis) and contrasting this with an alternative hypothesis of being within the “favorable” green zone [35]. A sample size is considered appropriate if it allows for ≥80% power to reject being in the red zone if the green zone holds true. For detailed information about this methodology, please consult Lewis et al. [36].

Progression parameters and their subsequent point estimates as described in Table 2 were used. Considering a one-tailed, one-sample binomial test based on normal approximation (with continuity correction) with α = 0.05, the following minimum sample sizes for each parameter were obtained:Feasibility of participant retention at post-intervention (Rul = 0.50 and Gll = 0.70)—41 participantsFeasibility of consent rate (Rul = 0.40 and Gll = 0.60)—42 participantsFeasibility of program completion (Rul = 0.45 and Gll = 0.75)—18 participants (intervention arm)Feasibility of program acceptability (Rul = 0.45 and Gll = 0.75)—19 participants (intervention arm)Feasibility of program fidelity (Rul = 0.40 and Gll = 0.70)—19 participants (intervention arm)

Therefore, a sample size of 42 participants, with 25 participants in the intervention arm, allows for ≥80% power to reject the null hypothesis for each of the feasibility outcomes. Moreover, this sample size is sufficient for the estimation of effect sizes for a future larger trial, as it allows for the collection of preliminary data needed to calculate reliable effect size estimates and assess the variability in psychological measures.

Regarding our qualitative data, according to the recommendations of Boddy [37] and van Risjnsoever [38], we aim to recruit 10 to 12 participants, as this sample size is often sufficient to achieve data saturation when the aim is to explore shared experiences within a relatively homogeneous group. Moreover, we will closely monitor data saturation during analysis and will adjust the sample size if necessary to ensure robust and meaningful findings.

**Table 2 healthcare-13-00176-t002:** Feasibility progression parameters.

Parameter	Thresholds		Justification
1. Feasibility of Retention of Families at Post-Intervention *Can a significant number of recruited families be retained until post-intervention?*	GREEN ZONE (Go—Proceed with full RCT)	>70%	Ensuring a substantial post-intervention retention rate is essential to obtain accurate and unbiased post-intervention data Favorable retention rates at the feasibility trial will contribute to estimating the required sample size for a larger RCT Systematic reviews have shown that attrition rates between 9 to 27% can be found in RCTs testing parenting interventions for childhood behavior problems [39] Previous trials of the BaP program reported an average retention rate of 80% [18,19]
	AMBER ZONE (Amend—Proceed with changes)	50–70%	
	RED ZONE (Stop—Do not proceed unless significant changes are made)	<50%	
2. Feasibility of Consent Rate *Is the rate of eligible families who consented and were randomized favorable for a large-scale RCT?*	GREEN ZONE (Go—Proceed with full RCT)	>60%	An adequate consent rate is essential for the feasibility trial to accurately estimate the number of families who need to be reached, in order to achieve the required sample size to obtain significant statistical power in a large-scale RCT. Low consent rates may provide important information regarding issues in recruitment procedures (such as locations of recruitment or information available to interested participants). Previous trials report an average consent rate of 70% [40] Previous trials of parenting interventions in Portugal report consent rates ranging from 63% to 97% [41,42] Previous studies of the BaP program report an average consent rate of 71% [19]
	AMBER ZONE (Amend—Proceed with changes)	40–60%	
	RED ZONE (Stop—Do not proceed unless significant changes are made)	<40%	
3. Feasibility of Program Completion *Can a significant number of participants from the intervention arm complete the BaP program?*	GREEN ZONE (Go—Proceed with full RCT)	>60%	Achieving favorable program completion rates is critical to obtain accurate and unbiased data A systematic review [43] found a mean program completion rate of 80% with a wide variety across studies between 50% and 100% Previous trials of the BaP program have shown an average completion rate of 70% [18,19]
	AMBER ZONE (Amend—Proceed with changes)	30–60%	
	RED ZONE (Stop—Do not proceed unless significant changes are made)	<30%	
4. Feasibility of Program Acceptability *Does an appropriate number of families from the intervention arm rate the BaP program acceptable?*	GREEN ZONE (Go—Proceed with full RCT)	>75%	Program acceptability is an important criterion in considering if the BaP program will be well received in the Portuguese community Program acceptability will be measured using the treatment acceptability rating scale (TARS) A total score of 27 or more equates to ratings of “Quite a lot” or “A great deal” on each item Previous trials of the BaP program found that an average of 98.5% of participants had total scores ≥ 27 [19] A conservative threshold of 75% will be used
	AMBER ZONE (Amend—Proceed with changes)	45–75%	
	RED ZONE (Stop—Do not proceed unless significant changes are made)	<45%	
5. Feasibility of Program Fidelity *Can the BaP intervention be delivered as planned?*	GREEN ZONE (Go—Proceed with full RCT)	>70%	For the BaP program, 75% fidelity is considered appropriate, which would mean that six out of eight sessions were delivered as planned Fidelity estimates serve as indicators to identify deviations from the designed intervention delivery, exposing potential issues like methodological challenges and variances with local contexts [44] Increasing fidelity correlates with improved outcomes [44] Conservative estimates of fidelity rates are used because this is the first time the BaP program will be tested in a Portuguese context, and thus, cultural and linguistic factors can significantly impact fidelity
	AMBER ZONE (Amend—Proceed with changes)	40–70%	
	RED ZONE (Stop—Do not proceed unless significant changes are made)	<40%	

